### Data analysis

All data analysis for the primary outcomes will be done on an intention to treat basis. As the baseline variables shown in Table 4 are known a priori to be associated with either of the two primary outcomes, they will be collected to ensure we adequately control for their potential confounding effects. In the secondary analysis, the outcomes will be adjusted for these confounding factors.

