**Methods/Design:**

The study is designed as a non-randomized multiple center cohort study including 12 sites in Germany and Austria. The inclusion period is planned to be 12 months with a follow up of 6 months. Allocation to operative or non-operative treatment is choosen by the patient together with his treating surgeon. The primary outcome is time to return to previous activity level adapted for loading of the wrist in daily life as measured by a newly developed questionnaire (PLDL-wrist). Factors identified a priori to be associated with the outcome, e.g., poverty status, age, education, smoking status, gender, and occupation, are measured to ensure adequate control for their potential confounding effects.

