**Discussion:**

The rationale and the design of a multiple center cohort study are presented. As it is not considered feasible to randomize patients in this study, potential confounding effects need to be controlled adequately.

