### Study design

The study is designed as a non-randomized cohort study, involving multiple sites with multiple surgeons and potentially differing patient populations. The chosen design implies a potential for bias and uncontrolled confounding. This will be addressed in the method of data collection and data analysis (see below). The eligibility criteria do only allow patients to be included, that do have isolated, complete fractures of the mid third of the scaphoid without signs of displacement or comminution visible in CT scan, while patients with any additional fracture of other sites are excluded, leading to a very homogenous injury pattern an thus minimizing residual "confounding by indication".

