### Treatment allocation

The decision on whether to choose an operative or non-operative treatment procedure is taken by the patient together with his treating surgeon. The participation in the study is completely independent of this decision and does not influence the choice of treatment procedure. Patients are classified as operative or non-operative according to the initial treatment decision taken during the first two weeks following injury.

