## Discussion

When planning the study, a randomized controlled trial was considered but as the participating surgeons, as well as patients, often have preferences for one of the two treatments under investigation, we decided to design this study as a prospective non-randomized cohort study. However, the design implies a potential for bias and uncontrolled confounding, which needs to be addressed in the method of data collection and data analysis.

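### Treatment is chosen by patient and surgeon, yet adjustment for confounders is left to the secondary analysis, so the primary comparison is unprotected

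*Protocol article*

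**What the plan says.** All references are to the protocol article.

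- **Allocation** (Treatment allocation): "The decision on whether to choose an operative or non-operative treatment procedure is taken by the patient together with his treating surgeon". The closing Discussion explains that a randomized trial was not chosen "as the participating surgeons, as well as patients, often have preferences for one of the two treatments under investigation".
- **Recognised risk** (Study design): "The chosen design implies a potential for bias and uncontrolled confounding". The same section says this will be dealt with in data collection and data analysis. The abstract's Discussion states: "As it is not considered feasible to randomize patients in this study, potential confounding effects need to be controlled adequately".
- **Design-stage control** (Study design): eligibility is limited to one fracture type, "leading to a very homogenous injury pattern an thus minimizing residual" confounding by indication.
- **Named confounders**: the abstract's Methods/Design lists factors, "e.g., poverty status, age, education, smoking status, gender, and occupation, are measured to ensure adequate control for their potential confounding effects". Data analysis says that the Table 4 variables "are known a priori to be associated with either of the two primary outcomes".
- **Place of adjustment** (Data analysis): the primary outcomes are given an intention-to-treat basis and nothing more. Then: "In the secondary analysis, the outcomes will be adjusted for these confounding factors".
- **Sizing** (Sample size calculation): a two-sided two-sample t-test for primary outcome (1) and a two-sided log-rank test for primary outcome (2). Neither makes any allowance for covariates.

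**The concern.** In a randomized trial, a crude primary test with an adjusted supporting analysis is sound, because allocation makes the groups comparable in expectation. That protection is absent here. Occupation, age and education can plausibly influence both the choice of surgery and the speed of return to work and household duties. The protocol itself names these variables as potential confounders.

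Two features of the plan might seem to fill the gap, but neither does:

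- Restricting entry to one fracture pattern limits confounding by injury severity. It does not balance poverty status, age, education, smoking, gender or occupation.
- Intention to treat, in this study, means classification by the initial treatment decision. It fixes who is counted in which group and does not make the groups comparable.

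What is at stake is the main conclusion, that surgery returns patients to activity sooner. If crude and adjusted results disagree, the plan gives precedence to the one exposed to the confounding it has itself identified.

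**Working it through.** **1. Reproduce the plan's sample size for primary outcome (1).** Inputs from Sample size calculation: difference 4 weeks, SD 5 weeks, two-sided alpha 0.05, power 90%, one cast patient to four operated patients, 25% loss.

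Cast patients needed (normal approximation):

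n = (1 + 1/4) × (1.960 + 1.282)² × 5² / 4² = 1.25 × 10.51 × 1.5625 ≈ 20.5, rounded up to 21. The screw group is then 4 × 21 = 84.

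Allowing for loss: 21/0.75 = 28 and 84/0.75 = 112. This matches the stated 28 and 112. Exact power from the noncentral t distribution at 84 and 21 is 0.901. The planned size is therefore that of an unadjusted t-test.

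The 92% log-rank power was not recomputed, because the survival figures in Table 3 are not in the text available.

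**2. Size of a plausible bias (assumption).** The documents give no covariate imbalance and no covariate effect. Take one binary confounder, for example manual work, and use bias = prevalence difference × effect on return time:

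- low: 0.20 × 3 weeks = 0.6 weeks, which is 0.6/4 = 15% of the target difference
- high: 0.30 × 5 weeks = 1.5 weeks, which is 1.5/4 = 37.5%, or about 38%

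**3. Effect on the crude test when treatment has no effect.** SE = 5 × √(1/84 + 1/21) = 1.22 weeks, df = 84 + 21 − 2 = 103, noncentrality = bias/SE.

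| Bias (weeks) | Two-sided rejection rate |
|---|---|
| 0 | 5% |
| 0.6 | 7.8% |
| 1.0 | 12.8% |
| 1.5 | 23.0% |
| 2.0 (beyond the assumed range) | 36.9% |

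The bias could also run the other way. With a true 4-week benefit and 1 week of bias towards the null, the expected difference is 3 weeks and power is about 68% instead of 90%.

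**4. Power of an adjusted primary analysis at 84 and 21.** If covariates explain a share R² of treatment choice, the variance of the treatment estimate is multiplied by 1/(1 − R²). If they also explain a share of outcome variance, it is multiplied by one minus that share. Degrees of freedom are kept at 103 for simplicity. The R² values are assumptions.

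| R² with treatment choice | Power, no outcome variance explained | Power, 20% of outcome variance explained |
|---|---|---|
| 0.1 | 0.869 | 0.931 |
| 0.2 | 0.828 | 0.901 |
| 0.3 | 0.776 | 0.860 |

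**The case against.** The strongest reply is that the article never states the primary analysis model. The t-test and log-rank test appear only as the basis for sizing, and sizing on a simple test does not bind the final model. The plan does exercise control: it restricts eligibility, measures confounders named in advance and commits to an adjusted analysis of the outcomes. Reporting a crude and then an adjusted estimate is a common order in cohort studies, and readers would see both. The bias figures are wholly assumed, and a single factor that shifts return by 3 to 5 weeks is about as strong as the treatment effect itself.

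Part of this stands. Control of confounding is not absent; the defect is which estimate comes first. The size and direction of bias are unknown, so the text supports saying that the primary comparison is unprotected against measured confounders, not that a given bias exists. The lower end of the assumed range does modest harm, at 7.8%.

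The core is not answered. The article assigns adjustment to the secondary analysis in so many words and nowhere assigns it to the primary one. This is therefore a stated rule and not a detail left to the analysis plan; an analysis plan that followed it would carry the problem forward. If the sponsor meant that the adjusted estimate leads, the sentence needs rewriting in any case.

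**Conclusion.** The concern holds, and the rule should be changed before analysis. A comparison with self-selected treatment is given a primary analysis without adjustment for variables that the protocol regards as known predictors of the outcome. This does not meet the protocol's own aim of adequate control.

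Under the assumed biases of 0.6 to 1.5 weeks, the nominal 5% test would reject a true null in about 8% to 23% of studies. Bias in the opposite direction would hide a real benefit. These figures rest on SD 5 weeks, 84 and 21 evaluable patients, and assumed confounder strength. The conclusion about the rule itself depends on none of them.

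**What to change.** Rewrite the Data analysis section so that the covariate-adjusted treatment effect is the primary analysis for each primary outcome:

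- For primary outcome (1), use a linear regression of time to the 80% threshold on treatment, a prespecified set of Table 4 variables and the baseline PLDL score, which is already collected.
- For primary outcome (2), use a time-to-event regression with the same prespecified Table 4 variables.
- Keep the covariate set short and fix it in advance. About 105 evaluable patients can support an outcome regression of moderate size, but with only about 21 in the cast group a large propensity model would be fragile.
- Report the unadjusted t-test and log-rank test as descriptive.
- State that the 90% and 92% power figures refer to the unadjusted tests, and that confounding by unmeasured factors remains possible.

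The change is one of wording and needs no new data. Its price is some power: from 90% to about 87% to 78% if covariates explain 10% to 30% of treatment choice and none of the outcome variance. If they also explain 20% of outcome variance, power is about 93% to 86%.

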## Discussion

When planning the study, a randomized controlled trial was considered but as the participating surgeons, as well as patients, often have preferences for one of the two treatments under investigation, we decided to design this study as a prospective non-randomized cohort study. However, the design implies a potential for bias and uncontrolled confounding, which needs to be addressed in the method of data collection and data analysis.

## Conclusion

The rationale and the design of a cohort study comparing the time to return to daily activities in patients with non-displaced scaphoid fractures receiving operative treatment versus patients receiving non-operative treatment has been presented.

## Abbreviations

CT – Computer tomography

DASH – Disability of the Arm, Shoulder and Hand questionnaire

DMQ – Dutch musculoskeletal questionnaire

PLDL-wrist – Questionnaire on physical loading of the wrist in daily life

QAS – Questionnaire on activity status

RCT – Randomized controlled trial

ROM – Range of motion

RTW – Return to work

SF-36 – Short form 36

VAS – Visual analog scale
